## Methods

### Overview

A randomized, parallel-arm, controlled, outcome measurer–blinded, and multicenter clinical trial conducted in 2 neurorehabilitation centers in Italy aims to investigate the effectiveness of AOT in patients with chronic stroke (ie, >6 months from the first event) using quantitative EEG biomarkers, confirming the translational power of a tailored treatment.

A total of 60 individuals who have been enrolled will be randomized to the experimental group in hospital (EG@Hosp), experimental group at home (EG@Home), or control group (CG) in a 1:1:1 ratio.

The EG@Hosp will observe and execute ADL that are task-oriented actions (AOT protocol); the EG@Home will observe and perform the same ADL at home (AOT protocol at home); and the CG will not observe any motor task videos (but will watch video only on landscapes and historical issues), and after verbal instructions, they will perform the same actions observed by the other 2 groups.

After completing the patient screening, randomization will be performed before the first treatment session (T0). At baseline (T0), midintervention (after the 7th session; T1), and after the intervention (15th session or 5th week; T2), outcomes (ie, clinical scales, EEG and electromyography [EMG] signals, and kinematic parameters) will be assessed to evaluate impairment and functional abilities.

For each group, the total duration of the intervention will be 5 weeks (3 times a week) for a total of 15 sessions. After the end of the intervention, a 2-month follow-up assessment period (T3) will be scheduled to assess the maintenance and long-term effects.

The primary outcome assessed at T2 will be assessed by the Fugl-Meyer Assessment-Upper Extremity (FMA-UE) scores.

The trials will be performed at 2 neurorehabilitation centers in Italy: IRCCS San Raffaele Roma Hospital in Rome and at Casa di Cura del Policlinico Hospital in Milan.

All the data will be recorded in electronic case report forms through the REDCap (Research Electronic Data Capture; Vanderbilt University) system, accessed on the web via the internet for data collection and management.

A specific route diagram is presented in Figure 1. The protocol for this study was developed in accordance with the Standard Protocol Items: Interventional Trial Recommendations guidelines (SPIRIT) [40].

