### Assessment: Primary and Secondary End Points

#### Overview

A thorough assessment of the clinical improvement in the functionality of the affected upper extremity will be performed using the FMA-UE (primary outcome), which will be combined with other clinical scales (secondary clinical outcomes).

In addition, the secondary instrumental outcomes (ie, EEG, EMG, and kinematics) will be included to verify neural plasticity and motor recovery using neurophysiological and kinematic parameters.

In addition, only for home-based treatment (EG@Home) group, the usability of the platform and the participants’ satisfaction with the services will be evaluated using a specific questionnaire (Technology Acceptance Model [TAM]) and a nonstructured interview.

The variables related to the secondary instrumental outcomes (ie, EEG, EMG, and kinematics) will be evaluated during the standardized pointing task described earlier.

All the data will be analyzed using MATLAB software (MathWorks Inc). Specifically, the EEG recordings will be preprocessed offline using the MATLAB’s toolbox called *EEGLAB* for artifact removal.

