#### Neurophysiological Biomarkers

The following biomarkers will be used in the study:

The EEG signal will be recorded (0.01-100 Hz band pass; sampling frequency: 1024 Hz) using 64 to 128 electrodes (high-density EEG, system 10-10 increased) during the pointing task (described earlier). Alpha (8-13 Hz), beta (14-30 Hz), and mu (8-13 Hz) bandwidths will be registered. EEG biomarkers will be ERD and ERS of alpha and beta rhythms, beta brain coherence, and mu rhythm suppression [47-50].Surface EMG signals from the activation of 2 pairs of agonist and antagonist muscles from 4 upper arm and shoulder muscles (brachial biceps, brachial triceps, anterior deltoid, and posterior deltoid) will be recorded. Dual Ag-AgCl snap electrodes with an interelectrode spacing of 2 cm will be used during the acquisitions. A standard procedure, in accordance with Surface ElectroMyoGraphy for the Noninvasive Assessment of Muscles recommendations [51], will be used for skin preparation and electrode placement. The reference electrode will be placed over the electrically neutral lateral wrist epicondyle. The outcome of this analysis will be the cocontraction index calculated during the initial portion (epoch) of the single pointing movement (forward and return movement will be analyzed separately), which is identified as the acceleration phase of the hand kinematics.

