#### Analysis of the Effectiveness

Analysis of the primary outcome (ie, functionality of the affected upper extremity) will be performed using the per-protocol principle. Treatment effects will be compared using a 2-way repeated ANOVA for clinical measurements, considering “time” (3 levels: T0, T1, and T2) as a within-subject factor and “group” (3 levels: EG@Hosp, EG@Home, and CG) as a between-subject factor.

In addition, the percentage of participants who passed the minimal clinically important differences of the FMA-UE will be compared using chi-square tests between the 3 groups.

The mean power across the assessment “time” (ie, T0 and T2) related to the action observation condition will be implemented in a mixed-design ANOVA to evaluate significant changes. A separate ANOVA will be performed to assess power changes in the stimuli selection data, using “treatment” (ie, EG@Hosp vs EG@Home vs CG) as the between-subjects factor and action as the within-subjects factor. To assess the predictive value of biomarkers for AOT effectiveness, an analysis of covariance (ANCOVA) will be performed considering the clinical data as the dependent variable, the “group” as a fixed factor, and the biomarkers as covariates.

Subsequently, to evaluate kinematic parameters recovery, a mixed design ANOVA will be implemented with “time” and “treatment” as within- and between-subjects factors, respectively.

The level of significance will be set at *P*<.05. For post hoc comparisons, the level of significance will be set at *P*<.017 after Bonferroni adjustment (.05/n; the number of comparisons, n=3) for the comparison of interaction effects. Cohen *d* will be calculated to determine the effect size of the change in scores for the behavioral motor outcomes between the groups. Immediate training effects (data from T0-T2) and the durability of training effects (data from T2-T3) will be separately investigated using mixed effect models.

Clinical-neurophysiological correlations will also be analyzed: the correlation between the ERD and factors such as the clinical scale score will be studied. To evaluate the differences in trends related to the clinical evolution of the patients, we will define a new variable to group the participants according to the presence or absence of relevant clinical improvements. The relevant clinical improvement will be defined by a clinical specialist for this purpose.

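### The EEG change test analyses mean power during action observation, whereas the EEG outcomes are defined as ERD/ERS, beta coherence and mu suppression during pointing; no between-arm test is specified for the biomarkers as defined

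*Protocol article*

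**What the plan says.** The section Neurophysiological Biomarkers fixes the EEG outcomes: "EEG biomarkers will be ERD and ERS of alpha and beta rhythms, beta brain coherence, and mu rhythm suppression". The Overview under Assessment: Primary and Secondary End Points fixes the task in which they are measured: "The variables related to the secondary instrumental outcomes (ie, EEG, EMG, and kinematics) will be evaluated during the standardized pointing task described earlier". Neurophysiological Biomarkers likewise places the EEG recording in the pointing task.

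Analysis of the Effectiveness contains these statements on EEG:

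- The change test: "The mean power across the assessment “time” (ie, T0 and T2) related to the action observation condition will be implemented in a mixed-design ANOVA".
- A second EEG analysis: "A separate ANOVA will be performed to assess power changes in the stimuli selection data". Its between-subjects factor is treatment (three arms) and its within-subjects factor is action; time is not a factor.
- The predictive analysis, an ANCOVA "considering the clinical data as the dependent variable, the “group” as a fixed factor, and the biomarkers as covariates".
- The correlation analysis: "the correlation between the ERD and factors such as the clinical scale score will be studied".

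One further sentence is general and lists no outcomes: "Immediate training effects (data from T0-T2) and the durability of training effects (data from T2-T3) will be separately investigated using mixed effect models".

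**The concern.** The endpoint definition and the test do not refer to the same quantity. ERD, ERS and mu suppression are event-related: each expresses a change in band power relative to a reference period. Coherence describes coupling between signals. Mean power, as the analysis section words it, has no stated band, reference or link to any of these. The condition changes as well, from pointing to action observation.

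The EEG biomarkers are not a side issue here. The Methods Overview says that the effectiveness of AOT is to be investigated with quantitative EEG biomarkers, and the first objective under Aims is to demonstrate neurophysiological change after AOT. If the endpoint as defined and the variable as tested are left to differ, the choice of EEG metric, band and condition for the between-arm comparison stays open until the data have been seen. A reader of the results could not tell whether the reported EEG comparison was the planned one.

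**Working it through.** No figure in the plan bears on this point. The sample size was calculated for FMA-UE only and neither supports nor weakens it. The check is therefore a comparison of the sections.

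**Step 1. Defined outcome against tested variable.**

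| Item | Outcome definition (assessment sections) | EEG change test (Analysis of the Effectiveness) |
|---|---|---|
| Variable | Alpha and beta ERD/ERS, beta coherence, mu suppression | Mean power, no band or reference given |
| Condition | Pointing task | Action observation |
| Between-subject factor | – | None named; a grouping factor is only implied by the term mixed-design |
| Within-subject factor | – | Time: T0 and T2 |

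The text of the assessment sections describes no EEG recording during action observation.

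**Step 2. Each role that the defined biomarkers have in the analysis section.**

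- Change test: not named; the variable is mean power.
- Second EEG ANOVA: not named; the variable is power. Arms are compared, but across actions and not over time.
- ANCOVA: named as covariates. The dependent variable is clinical, so this does not test whether the biomarkers differ between arms.
- Correlation: ERD only, against clinical scores. This is an association, not a comparison of arms.
- Mixed effect models: no outcome named.

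The number of analyses that name ERD/ERS, coherence or mu suppression as a dependent variable compared between arms is 0.

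**Step 3. Can the defined biomarkers be recovered from the stated test?** ERD, ERS and mu suppression are changes in band power, so they could be if mean power were meant as event-related power; the text does not say so. Beta coherence could not be, because band power at a site carries no information on coupling between sites.

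**Step 4. Comparison with the other outcome domains.** The same section names clinical measurements as the variable tested, with time and group as factors, and kinematic parameters as the variable tested, with time and treatment as factors. Only for EEG does the tested variable depart from the defined outcome.

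**Step 5. How many tests a matching plan would need.** Counting ERD and ERS separately in two bands gives 2 × 2 = 4 quantities. Adding beta coherence and mu suppression gives 4 + 1 + 1 = 6. With six unadjusted tests at .05, and assuming independence for illustration, the chance of at least one false positive is 1 − 0.95^6 = 1 − 0.735 = 0.265. A Bonferroni level would be .05/6 = .0083. These biomarkers are likely to be correlated, so 0.265 is only a guide to why the tests need a label or an adjustment.

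**The case against.** The strongest reply is that mean power is shorthand. ERD, ERS and mu suppression are all changes in band power, and the Background describes the group's earlier EEG work as suppression or desynchronization of rhythms. Nothing in the analysis section says that power is absolute. The general mixed-model sentence is not limited to clinical scales and could include the biomarkers. The article is also condensed, and epoch, reference window and normalisation can properly be left to a full protocol or SAP.

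Part of this stands. A reader might infer that the biomarkers are never compared between arms. The documents do not support that, because shorthand and the general mixed-model sentence both remain possible. What can be said is that no such test is specified. Nor should the change test be called a group-by-time test as if the text said so; the group factor is inferred.

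The reply does not remove the mismatch. The article does not leave the EEG test to another document: it states a variable, two time points and a condition, and the variable and condition differ from its own definitions. The section uses the term ERD by name a little later, so the term was available. Shorthand cannot cover beta coherence.

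Three further inferences are tempting and unsupported:

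- A drift in overall EEG amplitude could pass for a treatment effect. Arms are randomised, all assessments take place in hospital and assessors are blinded. Session-to-session gain that does not differ by arm adds noise and can cost power, but it does not create a false effect.
- Mean power is necessarily the noisier measure, with a power loss that can be quantified. Any such figure rests on assumed noise in the signal and in the reference period, and the documents give neither.
- Omitting T1 is an error. The Methods Overview does list EEG at T1, but a T0 to T2 contrast matches the primary time point and is a legitimate choice.

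**Conclusion.** Wrong as written, for a secondary outcome. The EEG outcomes are defined as one set of measures in one task, and the stated change test uses another measure in another condition without naming the arms as a factor. No between-arm test is specified for any of the EEG biomarkers as defined. For beta coherence none can be derived from the power analyses; for ERD/ERS and mu suppression one could be derived only by assuming that power means event-related power.

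The conclusion rests on the wording of the article alone and on the standard meaning of coherence as a coupling measure. It does not depend on any assumed effect size or noise level. It does not touch the primary FMA-UE analysis. Its weight comes from the place of these biomarkers in the first aim.

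**What to change.** In Analysis of the Effectiveness, make the biomarkers listed under Neurophysiological Biomarkers (alpha and beta ERD/ERS, mu suppression and beta coherence) the dependent variables of the mixed-design ANOVA. Name group (EG@Hosp, EG@Home, CG) as the between-subject factor and time (at least T0 and T2) as the within-subject factor. Keep mean power as a descriptive summary. If mean power was meant as event-related power, say so and tie it to the definitions.

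Reconcile the recording condition: the assessment sections say pointing and the analysis section says action observation. State which condition each EEG analysis uses and, if both are recorded, describe both. The reference period for the event-related measures is for the investigators to specify; the article gives none.

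The cost is a change of wording and some extra EEG processing. If the condition chosen is the one already recorded, no new data are needed. The drawback is a larger number of secondary EEG tests, up to six on the count above. Label them exploratory or adjust them for multiplicity, and state which before the data are analysed.

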### Aims

The project aims to achieve the following objectives: (1) induce functional modification of the cortical components underpinning the action organization, exploiting the peculiar features of the MNS and demonstrating the relevant clinical, kinematic, and neurophysiological changes after AOT—in particular, the analysis of the AOT effectiveness will also consider the predictive value of neurophysiological biomarkers; and (2) provide the home-based AOT program, to the best of our knowledge, for the first time in Italy, thereby rendering evidence-based considerations regarding the feasibility and impact of our home-based AOT program for future systematic application of the approach.

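### The ANCOVA meant to show which biomarkers predict AOT effectiveness has no group-by-biomarker term, so it tests prognosis and can mislabel a prognostic biomarker as predictive

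*Protocol article*

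**What the plan says.** The Aims section of the protocol article makes biomarker prediction part of the first objective: "the analysis of the AOT effectiveness will also consider the predictive value of neurophysiological biomarkers". The Abstract (Objective and Conclusions) and the Discussion repeat this.

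Analysis of the Effectiveness gives the question to one model. "To assess the predictive value of biomarkers for AOT effectiveness, an analysis of covariance (ANCOVA) will be performed", the sentence continuing "considering the clinical data as the dependent variable, the “group” as a fixed factor, and the biomarkers as covariates".

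The candidate biomarkers are listed under Neurophysiological Biomarkers: "EEG biomarkers will be ERD and ERS of alpha and beta rhythms, beta brain coherence, and mu rhythm suppression". The groups, from the Methods overview, are "experimental group in hospital (EG@Hosp), experimental group at home (EG@Home), or control group (CG) in a 1:1:1 ratio". The general threshold is "The level of significance will be set at *P*<.05".

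**The concern.** A biomarker is prognostic if it tracks outcome whatever the treatment. It is predictive of treatment effectiveness if the difference between treated and control participants changes with its level. Only the second property helps decide who should be offered AOT, and the article says it wants to support a tailored treatment.

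An ANCOVA with group and covariates as separate terms assumes equal covariate slopes in all arms. It therefore assumes away the quantity that its stated purpose requires. Control participants receive no action observation, but they do the same motor practice and continue conventional rehabilitation. A biomarker that follows recovery equally well in them says nothing about AOT.

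At stake is a headline claim. A biomarker that merely marks participants likely to do well could be reported as marking participants who respond to AOT. The reverse can also happen: a genuine modifier whose slopes cancel across arms would be missed.

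**Working it through.** **1. Is the interaction supplied elsewhere?** Three other parts of Analysis of the Effectiveness might seem to supply it.
- The Bonferroni sentence mentions interaction effects, but it governs post hoc comparisons. The only interaction the article names is group by time, in Sample Size.
- The correlation of ERD with clinical scores is an association and does not compare AOT with control.
- The grouping by presence or absence of relevant clinical improvement does not contrast AOT with control at different biomarker levels.

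None of these tests whether the AOT effect depends on a biomarker.

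**2. Inputs.**
- From Sample Size: 54 evaluable participants, 60 recruited, 3 groups. The dropout step reproduces: 54 / (1 − 0.10) = 60. The article gives no figure for the biomarker ANCOVA, and nothing below depends on how 54 was obtained.
- From Analysis of the Effectiveness: alpha 0.05.
- Assumed: the biomarker-outcome correlation r, from 0 to 0.6. The documents give none.

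**3. Models compared.**
- As written: outcome = group + β·biomarker. Test β = 0 (1 df).
- With interaction: outcome = group + β·biomarker + group × biomarker. Test equal slopes (2 df).

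**4. Purely prognostic biomarker.** Data were generated as outcome = r·b + √(1 − r²)·noise, with the same slope in all three arms, so the biomarker has no bearing on the AOT effect. There were 8,000 simulated trials per row.

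| Assumed r | Covariate significant, N = 54 | Covariate significant, N = 60 | Interaction significant (both N) |
|---|---|---|---|
| 0 | 5% | 5% | about 5% |
| 0.2 | 31% | 32% | about 5% |
| 0.3 | 60% | 64% | about 5% |
| 0.4 | 85% | 89% | about 5% |
| 0.5 | 97% | 98% | about 5% |
| 0.6 | 99.8% | >99.9% | about 5% |

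Hand check at r = 0.3, N = 54: noncentrality ≈ 0.3 / √(1 − 0.09) × √51 = 0.3145 × 7.141 = 2.25. Power ≈ Φ(2.25 − 1.96) = Φ(0.29) ≈ 0.61, in line with the simulated 60%.

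**5. True modifier with opposite slopes.** Take slopes of 0.3 in both AOT arms and −0.6 in control, residual SD 1. The pooled slope is (36 × 0.3 + 18 × (−0.6)) / 54 = 0. At N = 54 the additive model flags the biomarker in 7% of trials and the 2-df interaction test in 72%.

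**6. Power of the corrected test.** Take slopes of 0.5 SD in both AOT arms and 0 in control, N = 54. The 2-df interaction test has about 29% power. A 1-df contrast of the pooled AOT slope against the control slope does somewhat better: SE ≈ √(1/36 + 1/18) = 0.289, 0.5 / 0.289 = 1.73, and Φ(1.73 − 1.96) ≈ 0.41. This normal approximation is optimistic at this size; simulating the contrast gave about 37%. Either figure is low.

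**The case against.** **The percentages are the power of a test for an association built into the simulation.** This is true. They become an error rate only if a significant covariate is read as prediction of AOT benefit, and the article states no decision rule. But it gives the ANCOVA exactly that purpose and names no other term that could serve it.

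**The article may not write out its interactions.** For the primary repeated ANOVA it names only time and group, although Sample Size shows that group by time is the target. This lowers certainty a little. A factorial ANOVA includes its interaction by default, however, whereas an ANCOVA by default does not.

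**The authors may use the word predictive loosely.** The Background speaks of predictive value as a sign of neural plasticity, and the Discussion seeks biomarkers that can evaluate AOT effectiveness. If a response marker or a prognostic marker is meant, clearer wording is an adequate remedy. This stands, and it is why relabelling is offered below as an alternative.

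**Readings that go too far.** A reader might infer that every prognostic biomarker will be declared predictive. The table does not support that: the chance is 31% at r = 0.2. A reader might also infer that the plan enters a post-treatment biomarker, omits baseline FMA-UE or centre, or puts alpha and mu (both 8-13 Hz) into one model as near-duplicates. The article does not say which visit's biomarker is used, does not exclude further terms, and does not say that all biomarkers enter together. In a condensed article this is silence, not error.

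**Conclusion.** The mismatch is real. The article states a question about treatment effectiveness and a model that, on its plain reading, answers a question about prognosis. Since the model is stated, this is not a detail left to a fuller document.

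The structural point needs no numerical assumption. The size does: it rests on assumed r, equal slopes across arms, one biomarker tested at a time and normal errors.

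This should be fixed, but it is not a critical defect. A reader might take it to threaten the trial's main result. It does not: the primary FMA-UE comparison does not use this model, and the sample size was not set on the EEG biomarkers.

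**What to change.** Either of two changes resolves it.

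**Keep the predictive question.** Add a group by baseline (T0) biomarker term to the ANCOVA, with one biomarker per model. Name in advance the slope contrast of the two AOT arms against control as the term that carries the claim, so that hospital-versus-home slope differences do not enter it. Report that contrast with its confidence interval, call the biomarker main effect prognostic, and label the analysis exploratory.

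**Keep the additive model.** Describe the biomarkers as prognostic for outcome only, and drop statements that they predict AOT effectiveness.

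The cost is a wording change and, for the first option, one added interaction. EEG is already scheduled at T0, so no new data or participants are needed. The downside is low interaction power, so the first option will usually give a wide interval and a more cautious conclusion. A non-significant interaction should not be read as showing that a biomarker has no predictive value.

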### Sample Size

As the changes in the effects of upper limb AOT in patients with stroke on EEG biomarkers have not been previously investigated, we have estimated the sample size based on previously published studies [58,59], comparing AOT and conventional therapy. We estimated the sample size required to detect differences in the effects of “group”×“time” interactions on primary clinical outcome (FMA-UE).

For this outcome, an effect size of 0.495 [60,61] is expected based on previous studies. Given the expected effect size, a total sample size of 54 will be required for repeated ANOVA with a power of 0.8 and a 2-sided type-I error of 0.05 (number of groups=3 [ie, EG@Hosp, EG@Home, and CG]; number of measurements=3 [ie, T1, T2, and T3]). Therefore, when considering a dropout rate of 10%, we plan to recruit 20 participants for each group (a total of 60 participants) for this study.

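### The supplementary comparison of trends by clinical evolution reduces measured change to improved or not improved; using the continuous FMA-UE change is a cheap improvement

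*Protocol article*

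**What the plan says.** The last paragraph of Analysis of the Effectiveness concerns the link between neurophysiology and clinical status. It plans first that "the correlation between the ERD and factors such as the clinical scale score will be studied". It then turns to a second question: "To evaluate the differences in trends related to the clinical evolution of the patients", the plan is that "we will define a new variable to group the participants according to the presence or absence of relevant clinical improvements". On how improvement is judged it says only: "The relevant clinical improvement will be defined by a clinical specialist for this purpose". It names no scale, threshold or test for this variable.

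Earlier in the same section, the predictive value of the biomarkers is given its own analysis: "an analysis of covariance (ANCOVA) will be performed considering the clinical data as the dependent variable", with group as a fixed factor and the biomarkers as covariates. The section also compares the arms on the percentage of patients who pass the FMA-UE minimal clinically important difference.

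The Aims section states that "the analysis of the AOT effectiveness will also consider the predictive value of neurophysiological biomarkers". The Methods overview schedules clinical scales and EEG at T0, T1 and T2, with a follow-up assessment at T3.

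**The concern.** Clinical evolution is recorded on scales with many levels, at several visits. With two categories, a patient just above the cut is treated as different in kind from one just below it, and all differences within each category are lost. This happens wherever the cut is placed. The protocol gives no reason for the split here. The responder view already has its own place in the comparison of arms on the FMA-UE minimal clinically important difference.

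The trial is small and is sized on FMA-UE. No power is stated for any analysis linking EEG to clinical change. If the two-group comparison is tested, a moderate association is more likely to be missed, and a null result could be taken as evidence that biomarker trend and recovery are unrelated.

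**Working it through.** **1. The plan's own figure.** The protocol states no power for this analysis. The only sample-size figure is for the group-by-time interaction on FMA-UE: "a total sample size of 54 will be required for repeated ANOVA with a power of 0.8". Reading the effect size of 0.495 as Cohen's f, with numerator df = 4 and noncentrality λ = f²N = 0.495² × 54 = 13.2:

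- denominator df = N − 9 = 45 gives power 0.799;
- denominator df = 2(N − 3) = 102 gives power 0.825.

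So 54 is reproduced to within 2 patients on these readings. The usual repeated-measures formula, which uses the within-subject correlation, does not give 54, but that does not bear on this point. Allowing for 10% dropout, 54 / 0.9 = 60. I therefore use N = 54 to 60.

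**2. Inputs for the check.**

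- N = 54 to 60 (Sample Size section).
- Two-sided α = 0.05. The Sample Size section gives it as two-sided, and the 5% level is repeated in the sentence beginning "The level of significance will be set at".
- Correlation r between biomarker change and clinical change: **assumed**, 0.2 to 0.5 and then up to 0.6.
- Share of improvers p: **assumed**, 25% to 50% and then down to 10%.
- The grouping is **assumed** to be a cut of one scale's change, tested between the two groups.

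**3. Formulas.** On the full scale, by Fisher's z,

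power ≈ Φ(atanh(r)·√(N − 3) − 1.96), plus a negligible lower tail.

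Cutting one of two bivariate normal variables at improver share p attenuates the correlation to

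r′ = r·φ(z_p) / √(p(1 − p)).

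The factor is 0.798 at p = 50% and 0.734 at p = 25%.

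**4. Example at N = 54, r = 0.4.**

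- Full scale: atanh(0.4) = 0.424; × √51 = 3.03; − 1.96 = 1.07; power 85.7%.
- 50% improvers: r′ = 0.319; atanh = 0.331; × √51 = 2.36; − 1.96 = 0.40; power 65.6%.
- 25% improvers: r′ = 0.294; atanh = 0.303; × √51 = 2.16; − 1.96 = 0.20; power 58.0%.

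**5. Results at N = 54.**

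| assumed r | full scale | 50% improvers (loss) | 25% improvers (loss) |
|---|---|---|---|
| 0.2 | 30.5% | 21.0% (9.5) | 18.5% (12.0) |
| 0.3 | 59.9% | 41.4% (18.5) | 35.9% (24.0) |
| 0.4 | 85.7% | 65.6% (20.1) | 58.0% (27.7) |
| 0.5 | 97.5% | 85.4% (12.1) | 78.5% (19.0) |

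At N = 60, over the same ranges of r and p, the loss is 9.5 to 27.8 points. A simulation of bivariate normal data agrees closely. It gives slightly smaller losses in places, for example 7.9 points at N = 60, r = 0.5 and 50% improvers.

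**6. Wider range, by simulation.** The loss falls to 1.4 points (N = 60, r = 0.6, 50% improvers) and rises to 47.8 points (N = 54, r = 0.4, 10% improvers).

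**7. Efficiency.** At a 50/50 cut, 0.798² = 0.637, so 54 patients carry the information of about 0.637 × 54 = 34.

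**The case against.** The strongest objection is that the stated aim does not depend on this split. The predictive value of the biomarkers is assigned to the ANCOVA, which leaves the clinical outcome undichotomised, and the correlation of ERD with a clinical score also uses the measured scale. This stands, and it makes the comparison supplementary. A null two-group result would sit beside two other analyses. What remains is that the ANCOVA asks whether biomarkers predict clinical status, and the correlation names a score rather than a change and only ERD among the biomarkers. Neither asks how biomarker trend varies with measured clinical change.

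Second, the sentence names neither EEG nor FMA-UE. The EEG reading comes from the paragraph around it. FMA-UE is one of seven clinical scales, and where the section means the FMA-UE minimal clinically important difference it says so. A specialist's judgement across several scales would not be a cut of one variable, and the attenuation formula would not then apply as written. This also stands, so the figures are conditional.

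Third, no test is named, and the grouping may be meant only to describe. If so, no power is lost in a formal sense. The protocol does not say, and the proposed change keeps the descriptive use.

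Fourth, the calculation compares a correlation test with a two-sample test of a single change, not the time-trend analysis itself. It shows the order of the loss, not its exact size.

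**Conclusion.** The point holds as a cheap improvement. The protocol does reduce clinical evolution to two categories for this comparison, and measured information is discarded. If the grouping cuts a single scale's change and is tested, the loss is about 10 to 28 points of power for correlations of 0.2 to 0.5 and 25% to 50% improvers with 54 to 60 patients. It is about 1 to 48 points for correlations of 0.2 to 0.6 and 10% to 50% improvers. Both the correlation and the improver share are assumptions.

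A reader might infer more: that the biomarker aim as a whole rests on a dichotomised outcome, that the split is known to be made on FMA-UE change, or that 10 to 28 points is the plan's own loss. The document supports none of these. Two undichotomised analyses serve the biomarker question, the scale behind the split is not stated, and the size depends on inputs the protocol does not give.

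**What to change.** In the last paragraph of Analysis of the Effectiveness, make the inferential version of the trend comparison use the continuous T0-T2 change in FMA-UE. For each EEG biomarker, fit a mixed model with time, FMA-UE change, time × FMA-UE change and randomised group, and report the time × FMA-UE change coefficient with its confidence interval as the result. Keep the specialist-defined improved / not improved grouping as descriptive or supportive, for example in plots of the trends.

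The cost is a change of wording. The measurements are already scheduled, so no extra patients or visits are needed. The downside is that the model assumes an approximately linear relation, to be checked with residual plots, and a slope is slightly less simple to present than two groups. A gain beyond power is that the inferential result no longer depends on a definition of improvement still to be made.
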